### Primary physiological outcome measures

Electrocardiography (ECG) assessment from which HRV will be calculated at 10 weeks (short-term effect), in order to determine whether HRV-F results in improved autonomic nervous system function. HRV via ECG (electrodes on chest, modified lead II configuration) will be measured using the PowerLab 8/35 8-channel, 16-bit resolution recorder data acquisition system with programmable gain and two galvanically-isolated channels FE232 Dual Bio Amps (ADInstruments, www.adinstruments.com). A sampling rate of 512 Hz will be used for time/spectral analyses [4]. HRV signal processing will be performed using Kubios HRV Premium software (Version 3.3.1, University of Kuopio, Finland). HRV indexes neuro-cardiac function/regulation, generated by bidirectional heart-brain interactions (i.e., top-down influences on cardiac and peripheral physiological processes and bottom-up influences on central control mechanisms) and dynamic non-linear autonomic nervous system (ANS) regulation. HRV reflects the innervation of the heart by the sympathetic/parasympathetic divisions of the ANS [4]. In the time domain, average and standard deviation of the normal-to-normal intervals (SDNN; the variability of the heart) and root mean square of the successive differences (RMSSD, vagally mediated HRV) will be calculated. In the frequency domain, low frequency (LF), high frequency (HF, cardiac vagal control) and total power will be assessed. Details of a HRV protocol we have employed are available [40].
(ii)Functional transcranial doppler sonography (fTCD) to assess cerebral artery blood flow at 10 weeks (short-term effect), to determine cerebrovascular benefits associated with the HRV-F, using Multi-Dop T digital with QL routine software (Compumedics Limited, www.compumedics.com.au). fTCD assesses real-time cerebral blood flow velocities/circulation in basal cerebral arteries of the participants in response to the intervention [41]. fTCD is a reliable method for measuring cerebrovascular changes, provides high temporal resolution and is least susceptible to artefact than other imaging techniques [41].

Electrocardiography (ECG) assessment and Functional transcranial doppler sonography will be performed using the same instruments (as per primary outcomes) at 6 and 12 months (long-term effects).

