#### Assessment protocol

Primary and secondary physiological outcomes will be simultaneously recorded with participants sitting in their wheelchair, according to the following protocol: (i) resting phase of 5 min (after 2 min of habituation); (ii) mental challenge task (e.g. Stroop test) of 5 min; (iii) recovery phase of 5 min (resting and spontaneous breathing); (iv) breathing task of 5 min (paced breathing at 6 breath/min); 5-min recovery of 5 min (resting and spontaneous breathing). To control circadian influences, assessment will occur in the mornings (9 am-1 pm) and will be conducted in a quiet temperature-controlled room in the research laboratory. Participants will be asked to refrain from alcohol, caffeine and smoking at least 12 h before the assessment and to empty their bladder at the arrival to the laboratory.

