### Power analyses

For the primary outcome measures, assuming an α = 0.05, a small to moderate effect size of 0.3 (based on results from studies in other conditions), with 2 groups (HRV-F and control) of 50 in each group and four assessment periods, estimated statistical power is 0.99 [67]. To allow for reduced participant numbers due to loss to follow-up, sickness, death, or unwillingness to continue, we will recruit up to 120 participants.

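### The protocol makes five or six HRV indices plus Doppler flow jointly primary at one undivided alpha of 0.05, with no lead index, phase or success rule

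*Protocol article*

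**What the plan says.** Table 1 of the protocol article has three primary rows, all at baseline and 10 weeks: HRV time domain, HRV frequency domain and Doppler. The 6- and 12-month versions are secondary.

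The section on primary physiological outcome measures fills in the HRV rows. The time domain covers the average and standard deviation (SDNN) of the normal-to-normal intervals, and "root mean square of the successive differences (RMSSD, vagally mediated HRV) will be calculated". For the frequency domain: "In the frequency domain, low frequency (LF), high frequency (HF, cardiac vagal control) and total power will be assessed". Doppler is described as flow velocity in the basal cerebral arteries, with no artery or summary parameter singled out.

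The Assessment protocol section states: "Primary and secondary physiological outcomes will be simultaneously recorded with participants sitting in their wheelchair". It then sets out five 5-minute phases: rest, mental challenge (Stroop), recovery, paced breathing at 6 breaths per minute, and a second recovery. No phase is designated for the primary comparison.

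The Power analyses section opens "For the primary outcome measures, assuming an α = 0.05, a small to moderate effect size of 0.3" and continues "with 2 groups (HRV-F and control) of 50 in each group and four assessment periods, estimated statistical power is 0.99". The Statistical methods section plans linear mixed models for HRV and for blood flow, without naming a variable. No section gives an order of testing, a composite, a rule that all measures must succeed, or a division of alpha.

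**The concern.** Which variable is primary is something the protocol itself has to settle, and this one devotes a section and a table to it. What they settle on is a family. With five or six HRV indices and at least one Doppler measure on an equal footing, the reader cannot tell in advance which result would show that HRV-F works.

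The candidates also ask different questions. Paced breathing at 6 per minute is 6/60 = 0.1 Hz, inside the LF band of 0.04–0.15 Hz given in the Background. The Rationale section says slow resonant breathing, the skill that HRV-F trains, changes LF and total power. LF during the paced task may therefore reflect practice at that task, whereas an index from the resting phase reflects spontaneous autonomic regulation. As the text stands, either could be presented as the primary HRV result.

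At stake are the false-positive rate of the primary claim and the freedom to choose the leading index after results are known. The cost-effectiveness ratio has the same gap, because it is defined per increase in an unnamed time- and frequency-domain parameter.

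**Working it through.** **Inputs**
- Alpha 0.05, stated once for the primary measures together (Power analyses). Two-sided testing is an assumption; sidedness is not stated.
- 50 per group, four assessments, effect size 0.3, power 0.99 (Power analyses). The metric of 0.3 and the within-person correlation are not given.
- Size of the family k: 2 at the level of the abstract (HRV, Doppler), 3 by the rows of Table 1, and 7 by the primary-outcomes section (mean NN, SDNN, RMSSD, LF, HF, total power, and one Doppler measure). If mean NN is not a separate index, k = 6.
- Correlation between test statistics: not given; 0, 0.5 and 0.8 assumed.

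**The plan's own figure.** Read as Cohen's f = 0.3 with N = 100, four assessments and within-person correlation 0.3, the between-group noncentrality is 0.3² × 100 × 4 / (1 + 3 × 0.3) = 36/1.9 = 18.9 on 1 and 98 degrees of freedom, which gives power 0.991. The group-by-time test on the same f exceeds 0.999 for correlations from 0 to 0.8. So 0.99 can be reproduced, but only for one test at the full 0.05 using four assessments. Read as d = 0.3 at a single time point, power is 0.32.

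**Chance of at least one false positive if each measure is tested at 0.05 and any one counts.** For independent tests this is 1 − 0.95^k. For correlated tests it was simulated with equally correlated normal statistics.

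| k | independent | correlation 0.5 | correlation 0.8 |
|---|---|---|---|
| 2 | 9.75% | 9.0% | 7.8% |
| 3 | 14.3% | 12.6% | 9.8% |
| 6 | 26.5% | 20.7% | 13.8% |
| 7 | 30.2% | 23.0% | 14.9% |

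An alternative structure, with the six HRV indices correlated with each other at 0.3 to 0.9 and Doppler nearly separate (0 to 0.2), gives 27.8% down to 15.1% for k = 7.

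**Power cost of splitting alpha between two named measures.** Assume a baseline-adjusted comparison at 10 weeks, 50 per group and baseline correlation 0.5. The noncentrality is d/√(1 − 0.5²) × √(50/2).
- d = 0.6 (equivalent to f = 0.3 for two equal groups): noncentrality 3.46; power 93% at 0.05 and 88% at 0.025.
- d = 0.3: noncentrality 1.73; power 40% at 0.05 and 30% at 0.025.

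**The case against.** The strongest reply is that this is a condensed article. Multiplicity methods and derived-variable definitions often sit in a statistical analysis plan, and the HRV paragraph refers to a separate published protocol for detail. That stands for the adjustment method: its absence alone would not be a finding. It does not answer the main point, because the article itself designates the primary outcomes and designates a family.

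A second reply is that the alpha of 0.05 is an input to a power calculation and not a decision rule. That also stands. A reader might infer that one significant index in any phase would be declared a success, but the protocol does not say so. It states no success rule at all, and if every measure had to be positive the error would not exceed 5%.

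A reader might also multiply seven measures by five phases and arrive at 35 primary tests, with an error of 1 − 0.95^35 = 83%. The document does not support that as a plan. The phases describe how signals are recorded, and nothing says that each is a separate primary test. Independence is also implausible for indices taken from the same recording, some of which overlap in what they measure.

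Finally, the count of six HRV indices depends on reading the average NN interval as an outcome in its own right. Dropping it moves the independent figure only from 30.2% to 26.5%.

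**Conclusion.** The concern holds as a primary endpoint that the protocol fixes badly: several measures share primary status at one undivided alpha, with no lead index, phase, Doppler parameter or success rule. If each is tested at two-sided 0.05 and any positive result counts, the false-positive chance is about 8–10% for two measures and about 15–30% for seven. The success rule, the sidedness and the correlations (0.8 to 0) are assumptions, since the document gives none of them. Every case computed under that rule is above 5%. Leaving the phase open adds further room for choice, whose size cannot be fixed from the document. The stated power of 0.99 offers no reassurance here, because it describes one test over four assessments, not a family at 10 weeks.

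**What to change.** Before any outcome data are seen, name one HRV index in one recording phase at 10 weeks, and one Doppler parameter in a named artery in the same phase. The investigators should choose the index to match their question. The Rationale section points to LF or total power as the mechanism, while a resting, spontaneous-breathing phase avoids measuring practice at the paced task. Test the two in a fixed order or with Holm at an overall 0.05. Move all other indices and phases to secondary, and use the named index in the cost-effectiveness ratio.

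No data collection changes. The price is that the other indices can no longer support a primary claim. Fixed order costs the first test no power, but the second can be claimed only if the first succeeds. Holm's worst case, testing at 0.025, lowers power from 93% to 88% if d = 0.6, a value the protocol does not state, or from 40% to 30% if the stated 0.3 is read as d. The metric of the 0.3 should therefore be stated when the choice is made.

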### Secondary physiological outcome measures

#### Electroencephalography (EEG), electrooculography (EOG), respiration/breath rate, skin conductance, blood volume pulse and finger temperature

To measure these secondary outcome measures, two FlexComp electrophysiological monitoring systems (each having 10-channels each; Thought Technology, Ltd., Canada, www.thoughttechnology.com) with BioGraph Infiniti software, will be used for data acquisition of EEG (11 channels using International 10–20 montage system: F3, Fz, F4, C3, Cz, C4, P3, Pz, P4, O1, O2), skin conductance (2 channels, right and left hand), blood volume pulse (2 channels, right and left hand), EOG (1 channel), respiration (1 channel) and peripheral skin temperature (2 channels, right and left hand). The FlexComp has a sampling rate of 2048 samples/sec with 14 bits of resolution (1 part in 16,364). EEG will be used to assess change in brain wave activity in response to the HRV-F and will be spectrally analysed using fast Fourier Transform and a Hanning Window. Sophisticated noise/artefact removal strategies will be used to improve noise:signal ratio [31]. EOG will be used as a physiological measure of fatigue [40]. Skin conductance, blood volume pulse and finger temperature will assess sympathetic arousal and respiration breath rate [42].

#### Near infrared spectroscopy

The Brite MKII 27-channel functional near infrared spectroscopy (fNIRS) system (Artinis Medical Instruments B.V., Amsterdam, Netherlands) will be used to quantify brain oxygenation and neurological activation associated with the HRV-F intervention and complement the EEG measures. NIRS data analysis will be via the OxySoft (Artinis Medical Instruments B.V., Amsterdam, Netherlands) dedicated software used to collect, store, view, and analyse all NIRS signals [43].

#### Continuous blood pressure

Human NIBP Nano Foundation System (ADInstruments, www.adinstruments.com) will be used to record continuous blood pressure (BP) via non-invasive dual finger cuff system (Labchart software). This will ensure measurements of systolic and diastolic BP as well as BP variability (BPV), to quantify cardiovascular benefits associated with the HRV-F. Time series and spectral analysis of BPV and HRV will be used to evaluate baroreflex function/sensitivity and overall (cardiovascular) autonomic balance, with LF HRV indexing sympathetic activity and HF-HRV indexing cardiac vagal control.

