The presumed mechanism for benefits associated with self-regulation of the autonomic nervous system involves a combination of physiological processes resulting in strengthening of baroreflex homeostasis, vagal afferent pathways, and phase relationships between blood pressure, heart-rate and brain connectivity [19–22]. Optimal autonomic regulation is associated with healthy functioning of the body’s major systems, particularly cardiac and brain function (e.g., cognitive and psychological aspects) [11, 19–22]. Following a SCI, serious cardiovascular complications are a major concern, such as unstable blood pressure control related to episodes of orthostatic hypotension and autonomic dysreflexia (AD), characterized by critical blood pressure rises and associated bradycardia [23–25]. Benefits of improved autonomic self-regulation could therefore be substantial for people with SCI, including reduced cardiovascular morbidity associated with autonomic aetiology, orthostatic instability, severity of AD, and improved cognitive functioning, mental health, pain, vitality and sleep [4, 11–13]. Furthermore, this study may lead to improved understanding of the physiological underpinning of brain-autonomic dysfunction and the influence of top down/bottom up controls related to neuroplasticity [22].

Evidence that autonomic activity changes after a SCI and during autonomic challenges suggests autonomic modulation may be a new frontier for improving neuro-cardiac function in individuals with SCI and may mitigate maladaptive plasticity [11]. Underlying hypotheses are the development of intrinsic spinal rhythmicity within the injured cord or recovery of supraspinal pathways [22], demonstrating that autonomic activity measured by HRV in adults with SCI is imbalanced, very different to able-bodied individuals [26]. For example, groups with tetraplegia and paraplegia both have significantly reduced low frequency (LF) HRV activity and impaired sympatho-vagal control [26] and this autonomic imbalance was associated with sleep disorder and fatigue in SCI [4, 26, 27]. It has also been shown that after participating in a 40-min resting/cognitive task, adults with high lesions (at/above T3 level) significantly increased the standard deviation of the average normal-to-normal intervals (SDNN) in the HRV in the LF band (0.04–0.15 Hz) in comparison to an able-bodied cohort [4], suggesting that low frequency autonomic activity in this group is modifiable.

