### HRV-F protocol and rationale

#### Rationale

HRV-F is designed to improve autonomic and neurocardiac functioning using computer-based feedback of HRV and controlled diaphragmatic slow breathing around 3–7 breaths per minute. One goal of HRV biofeedback is to stimulate the baroreflex and enhance respiratory sinus arrhythmia (RSA), which involves fluctuations in heart-beat intervals linked with respiration, associated with variations of the parasympathetic cardiac signal [37]. That is, cognition and brain neural activity to adhere to a paced respiration rate and depth, evoking resonant frequency changes to RSA in LF HRV and Total HRV power (in the spectral bands). RSA amplitude (peak-to-trough heart rate difference across the breathing cycle) is contingent with slow breathing [37] and establishing resonant breathing frequency (generally lying between 4 and 7 breaths per minute), identifies the breath rate that is associated with largest gains in RSA and baroreflex activity [37]. Slow breathing rates, and especially breathing at the resonant breath rate, optimally stimulates the baroreflex, resulting in increased RSA and HRV, which is believed to be associated with healthy autonomic and cardiovascular systems [37].

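### The trained breathing response is expected in the LF band, yet the protocol reads LF as sympathetic and HF as vagal, so a working intervention would be misread

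*Protocol article*

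**What the plan says.** Five places in the protocol article bear on this point.

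- **Rationale (HRV-F protocol and rationale).** Training uses "controlled diaphragmatic slow breathing around 3–7 breaths per minute", with the resonant rate "generally lying between 4 and 7 breaths per minute". RSA is linked to the parasympathetic cardiac signal, and the training is described as "evoking resonant frequency changes to RSA in LF HRV and Total HRV power (in the spectral bands").
- **Background.** The band limits are given when a cited study in this population is described: "in the LF band (0.04–0.15 Hz"). Reduced LF activity is named there as part of the deficit after spinal cord injury.
- **Primary physiological outcome measures.** SDNN, RMSSD, LF, HF and total power at 10 weeks form the HRV part of the primary outcome. HF is labelled as cardiac vagal control; LF carries no label.
- **Continuous blood pressure.** Autonomic balance is to be evaluated from blood pressure and heart rate variability, "with LF HRV indexing sympathetic activity and HF-HRV indexing cardiac vagal control".
- **Economic evaluation.** Cost-effectiveness ratios are taken per increase in the time- and frequency-domain parameters.

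The recording has five 5-minute phases: rest, Stroop task, recovery, a paced task and a second recovery. Rest and both recoveries use spontaneous breathing. The paced phase is described under Assessment protocol as a "breathing task of 5 min (paced breathing at 6 breath/min"). Respiration is recorded on one channel as a secondary measure.

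**The concern.** The Rationale and the blood pressure section give opposite meanings to the same quantity. In the Rationale, a rise in LF is the parasympathetic response that the intervention is meant to produce. In the blood pressure section, a rise in LF is sympathetic activity, and a fall in HF is loss of vagal control. If trained participants breathe slowly while being recorded, their respiratory variability moves from HF into LF. An analyst who follows the blood pressure section would then report the intended effect as a shift towards sympathetic dominance.

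The label stands in a secondary-outcome section, but LF and HF are primary measures and HF carries its vagal label there too. The economic section adds a third reading, in which any increase is a gain, so a rise in LF counts as benefit and a fall in HF as loss. What is at stake is the conclusion drawn from the frequency-domain part of the primary outcome.

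**Working it through.** **Step 1: band arithmetic.** Inputs are the LF limits (Background), the trained rates (Rationale) and the paced rate (Assessment protocol). Frequency in Hz = breaths per minute / 60.

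- LF limits: 0.04 × 60 = 2.4 and 0.15 × 60 = 9.0 breaths/min.
- Trained range: 3/60 = 0.050 Hz and 7/60 = 0.117 Hz.
- Resonant range: 4/60 = 0.067 Hz and 7/60 = 0.117 Hz.
- Paced task: 6/60 = 0.100 Hz.

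Every trained rate, and the paced task, lies inside LF. Breathing above 9/min leaves RSA in HF; breathing below it puts RSA in LF.

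**Step 2: what a pure change of rate does.** This is an illustration. The following values are assumptions and are not in the protocol: RSA as a sine wave of amplitude 30 ms at the breathing rate, a second oscillation of 15 ms at 0.095 Hz, white noise with SD 10 ms sampled at 4 Hz, and HF taken as 0.15–0.40 Hz. RSA amplitude is held fixed and only the rate changes.

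A sine wave of amplitude A has variance A²/2, so RSA contributes 30²/2 = 450 ms² and the slow oscillation 15²/2 = 112.5 ms². The noise variance of 100 ms² spreads over 0–2 Hz. It gives 100 × 0.11/2 = 5.5 ms² in LF and 100 × 0.25/2 = 12.5 ms² in HF.

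| Breathing rate | LF (ms²) | HF (ms²) |
|---|---|---|
| Above 9/min | 112.5 + 5.5 = 118 | 450 + 12.5 = 462.5 |
| Below 9/min | 112.5 + 450 + 5.5 = 568 | 12.5 |

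SDNN is √(450 + 112.5 + 100) = 25.7 ms in both rows. A simulation of 5-minute records agrees: at 10–15/min LF was about 118 and HF about 462; at 3–8/min LF was 553–570 and HF about 12; SDNN was 25.6–25.8 ms throughout. At exactly 9/min the power is split (LF 441, HF 140).

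**Step 3: apply the labels.** Under the blood pressure section, the move from the first row to the second is a large sympathetic rise and an almost complete loss of vagal control. RSA amplitude, which the Rationale ties to the parasympathetic signal, has not changed.

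**Step 4: phase by phase.** In rest and recovery, the misreading of a rate change needs breathing to fall below about 9/min. In the 6/min task both arms are paced alike, so a difference in rate between arms is largely removed. Only the label fails there, because RSA sits at 0.100 Hz in everyone who follows the pacing.

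**The case against.** The strongest reply is that none of this shows a biased treatment comparison. A reader might infer that the arms will differ systematically in breathing at 10 weeks, since the HRV-F arm is asked to practise twice daily for about 20 minutes. The documents do not support that as a fact: they give no resting rates and do not say that trained participants will breathe below 9/min when unprompted. Slower breathing also lies on the intervention's pathway, so a difference produced through it belongs to the total intention-to-treat effect. On the Rationale's own account, slow breathing stimulates the baroreflex and raises RSA, so a rise in LF may be partly real benefit. All of this stands, and it confines the point to interpretation.

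It can also be said that the Background treats low LF as the deficit and the economic section counts increases as gains, so the direction for LF is implied. That is fair for LF taken alone. It leaves the sympathetic label unexplained and gives no way to read a fall in HF that accompanies a rise in LF.

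The article does not name the phase that supplies the primary value. The analysis plan may do so, and that silence is not counted here as a fault.

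A reader might further infer that breathing practice on the morning of testing contaminates the recording, because the restrictions cover only alcohol, caffeine and smoking. The within-session change cited in the Background followed a 40-minute resting/cognitive task in high lesions and says nothing about carry-over from breathing practice. That inference is not supported.

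**Conclusion.** The contradiction is real and rests on the printed text and simple arithmetic: trained rates of 0.050–0.117 Hz lie wholly within an LF band of 0.04–0.15 Hz. The Rationale assigns the response there to the parasympathetic side, and the blood pressure section assigns it to the sympathetic side. Followed as written, the latter would misread a working intervention on measures that are part of the primary outcome.

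The size of any shift in this trial is unknown. The illustrative figures depend on assumed amplitudes and on breathing crossing 9/min, and they show direction and mechanism only. SDNN and total power are not split at 0.15 Hz, so they escape this relabelling, though slow breathing may change them in other ways. The point should be corrected before the data are interpreted; it does not make the data unusable.

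**What to change.** 1. Reconcile Rationale, Primary physiological outcome measures, Continuous blood pressure and Economic evaluation so that LF and HF have one meaning throughout.
2. Withdraw the reading of LF as a sympathetic index, and of HF as a vagal index when breathing is at or below 9/min.
3. State in advance which direction of LF change and of HF change counts as improvement, and use the same direction in the cost-effectiveness ratios.
4. Base the primary HRV reading on the spontaneous-breathing resting phase (Activity #1), and read the 6/min phase separately.
5. Report breath rate by arm and phase, from the respiration channel already recorded, next to LF and HF. Use it as an aid to interpretation and do not adjust the primary intention-to-treat effect for it.

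Two tempting remedies are better avoided. Restricting the analysis to recordings above 9/min selects on a post-randomisation variable that treatment may affect. Moving to an unspecified time-domain measure may not help: for RSA of fixed amplitude, RMSSD is proportional to sin(π × f × RR). With RR assumed to be 0.9 s, this falls from 0.649 at 15/min to 0.279 at 6/min, a drop of 1 − 0.279/0.649 = 57% from rate alone.

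The cost is wording, a little more reporting and a less specific sympathetic/vagal interpretation of LF and HF. No new equipment is needed.
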